## Methods

### Study design

RADAR-MDD is a multi-centre prospective observational cohort study in which 600 individuals with a recent history of MDD will be asked to download several RMT apps and use an activity tracker for up to 2 years of follow-up. The study involves no randomisation or intervention, and uses commercially available activity trackers and smartphone sensors.

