### Study population

An estimated 100 relapses are required in order to provide sufficient power on which to test the predictive utility of RMT, if 10 variables were entered into the predictive model [32]. With an approximated annual relapse rate of 33% (a lower estimate than that provided in the Star*D trial; [33]), 300 participants would be required, followed-up for one year. Although there is evidence to suggest promising uptake to RMT protocols, the attrition rate in this length of follow-up is unknown, there are likely to be missing data, data are inherently “noisy”, and the relapse rate in our population may be lower than anticipated. We therefore aim to recruit a total of 600 individuals with a history of MDD across three research sites.

The eligibility criteria for inclusion in this study are summarised in Table 1. To recruit people at risk of relapse during the follow-up period, people with a recent history of MDD, with indication of a recurring trajectory will be approached to participate. No limitations have been applied regarding any treatment they may be receiving, although medication use and other psychological interventions will be monitored throughout the course of follow-up. Additionally, participants will be eligible to participate regardless of whether they are currently experiencing depression symptoms or not.

**Table 1 Tab1:** Eligibility criteria for participation in RADAR-MDD

Inclusion criteria	Exclusion criteria
Meet DSM-5 diagnostic criteria for diagnosis of non-psychotic MDD within the past 2 years. Recurrent MDD (a lifetime history of at least 2 episodes of depression; (LIDAS) [34]). Willing and able to complete self-reported assessments via smartphone. Able to give informed consent for participation. Fluent in English, Spanish, Catalan or Dutch language Existing ownership of Android smartphone or willingness to use an Android smartphone as their only smartphone. Aged 18 or over	Lifetime history of bipolar disorder, schizophrenia, MDD with psychotic features, schizoaffective disorders. Dementia History of moderate to severe drug or alcohol dependence within the last 6 months History of major medical disease which might impact upon the patient’s ability to participate in normal daily activities for more than 2 weeks (e.g. due to likely hospitalisations or other periods of indisposition). Pregnancy

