### Adverse events and study withdrawal

It is not expected that participation in RADAR-MDD will increase the risk of relapse, nor of there being other significant risks of harm to participants. There may be several reasons for withdrawal from the study:Participant choosing to no longer participate; participants will be informed both in writing and verbally that participation is voluntary, that non-participation will not influence their medical care, and that they are free to withdraw from the study at any point without providing reasons.The research team may withdraw the participant in the event of inter-current illness, adverse event (AE), protocol violation, administrative or other reasons.The participant loses capacity for continued participation.

In the case of participant self-withdrawal, all attempts will be made to follow-up with the participant to establish cause of withdrawal, and to collect qualitative data regarding experience of participation. Depressive relapse itself will not be cause for automatic withdrawal; unless they choose to stop, participants who are identified as experiencing a relapse will continue to participate until study end-point. All data, including those from withdrawn participants (unless they request for their data to be deleted), will be included in the final analysis. If a participant withdraws from the study prematurely without providing evaluable data, a replacement participant will be sought if resources allow.

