### Statistical and analysis plan

Descriptive statistics for demographics, attrition rate, and number of participants using the remote assessment measurements without loss or damage and providing adequate data for the duration of the study period will be estimated. Using classification/regression approaches, we will investigate whether any demographics and/or other numerical information obtained during baseline of the study might serve as a predictor for subjects drop out/percentage of adequate data. Using mixed-effect models with participants as random factor, we will estimate whether relationships between the amount of usable data during the weeks prior to the outcome assessment and obtained scale’s measurements exist.

Aggregated features obtained from biosensors, smartphones, cognitive tests and from ESM, as well as their changes from baseline or previous time points (delta features) will be used for statistical analysis. Aggregation will be done for the period of 2 weeks prior to participant’s evaluation with PHQ8 or longer time interval preceding 3-mothly outcome scale assessment, since relapse identification is done retrospectively. First, univariate approach, where each variable/feature will be modelled with use of mixed-effect models, with depressive relapse as fixed and participant as random effect, to find out which variables are influenced during the relapse. Demographics and other baseline characteristics will be added to the model, when necessary, with correction for multiple comparisons.

Secondly, we will construct predictive models, using aggregated data obtained prior to assessment of relapses and their changes from previous time points to predict binary (relapsed or not) or continuous (when scale score is treated as continuous variable) outcomes. Under assumption that data are missing at random, multiple imputation will be applied for covariates, where missing-ness is not drastically high. Multivariate prediction model will be constructed and variable selection, based on, for example, LASSO L1-regularization for linear models, or different feature selection algorithms will be applied. Models’ performance will be characterized through the cross-validation, putting stress on sensitivity and specificity of relapse prediction model.

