## Discussion

There is substantial evidence to suggest that changes in physical activity, sleep, stress, prosodic features, cognitive function, mood and sociability are associated with an increased risk of relapse [9–13]. RMT provides a new and unobtrusive way of measuring these variables, using smartphones and wearable technology to collect data reflective of participants’ daily lives and clinical symptoms. RADAR-MDD is the largest study to investigate multimodal RMT in a clinical cohort. If RADAR-MDD demonstrates that RMT is feasible to use in large populations, acceptable for participants, and provides clinically useful data, it may represent that start of a paradigm shift in how clinical data are collected and respective change in how health services are delivered [54]. The RADAR-CNS platform is a device-agnostic system and could be applied to any diagnosis or incorporated into any study design, potentially transforming data collection for clinical and research purposes.

However, to ensure translation into health services, extensive work is required to identify the RMT biosignatures most useful to assist in early detection of deterioration, and to understand the potential barriers and facilitators of large-scale uptake. There are anticipated challenges to this novel method of data collection. Firstly, change in health status may be a key barrier to long-term engagement with this study [30]; an exacerbation of depressive symptoms may influence ongoing participation rate throughout the duration of follow-up, and participant drop-out may represent a depressive relapse. However, there is also some evidence to suggest that people experiencing more severe symptoms may participate more fully, as they may be more motivated to improve their understanding of their condition [55]. Secondly, whilst this is a non-interventional study, encouraging individuals to monitor their own health and providing feedback on activity and sleep (via the FitBit app) may prompt people to change their behaviours or seek help sooner, reducing risk of relapse. There is also evidence to suggest that encouraging health monitoring may increase health anxiety, which in turn may contribute to worsening depressive symptoms [31].

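### The relapse model fixes neither the unit of analysis nor who is at risk, so continuing episodes can be scored as new relapses and relapse-driven drop-out is left unaddressed

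*Protocol article*

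**What the plan says.** The protocol article's *Statistical and analysis plan* sets the prediction models "to predict binary (relapsed or not") outcomes, or continuous ones where a scale score is modelled instead. Features are aggregated over the two weeks before a PHQ8 or over a "longer time interval preceding 3-mothly outcome scale assessment", together with their changes from earlier time points. The companion univariate models carry participant as a random effect. On missing data the section says: "Under assumption that data are missing at random, multiple imputation will be applied for covariates", provided missingness is not too high. No method is stated for a missing relapse outcome.

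Other sections bear on this:

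- *Primary outcome*: relapse is operationalised as MDD being present on the CIDI-SF with an IDS-SR score above 25. Prior remission is not required. A confirmatory interview follows a positive result.
- *Study population*: people may join whether or not they have current symptoms, and "the attrition rate in this length of follow-up is unknown".
- *Study design*: participants are to "use an activity tracker for up to 2 years of follow-up".
- *Adverse events and study withdrawal*: relapse does not end participation. "All data, including those from withdrawn participants" are kept for the final analysis unless deletion is requested.
- *Secondary outcomes*: remission is defined as an IDS-SR score below 14 without CIDI-SF MDD.
- *Discussion*: "participant drop-out may represent a depressive relapse", although people with more severe symptoms may also take part more fully.

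**The concern.** Predicting relapse means predicting a move from not being in an episode to being in one. The plan's label records a state, not a move, and no rule restricts the rows to people who could make that move. If intervals inside a continuing episode count as relapses, features that mark being depressed will look like features that foretell becoming depressed. The delta features suffer too: a change between two points within one episode is pooled with a change from well to ill.

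The second issue is the unseen outcome. If some people leave because they relapse, the positive rows most relevant to early detection are missing, and imputing covariates does not restore them. Both issues affect the third study objective and the sensitivity and specificity by which the plan will judge the model.

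**Working it through.** **The plan's own figure.** 100 relapses for 10 variables is 100/10 = 10 events per variable. At 33% a year, 100/0.33 = 303 participants, against the stated 300 (300 × 0.33 = 99 events). The figure reproduces. It counts one relapse per person, whereas the feature windows are tied to assessments, so the article does not settle the unit.

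**Reading A: one label per attended assessment (the more natural one).**

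*Continuing episodes.* Table 2 schedules the relapse measure at baseline and the *Outcome measurements* section repeats it every 3 months. Take an episode positive at k successive assessments after a true onset. One row is the onset and k − 1 rows are continuation, so the non-onset share is (k − 1)/k:

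- k = 2: 1/2 = 50%
- k = 3: 2/3 = 67%

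For an episode already present at baseline, every later positive row within it is continuation. The documents give no episode durations, so k is an assumption. In the k = 3 case, a model that flagged every continuation row and missed every onset would show a sensitivity of 67%. Continuation rows would also count towards the 100 events without being relapses.

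*Relapse-driven drop-out.* Hazard = −ln(1 − 0.33) = 0.4005 per year, so the 3-month risk is 1 − exp(−0.4005/4) = 9.5%. Assume that 30% of relapse intervals and 5% of non-relapse intervals go unobserved. Observed risk = 0.70 × 0.0953 / (0.70 × 0.0953 + 0.95 × 0.9047) = 0.0667/0.9262 = 7.2%, about 24% too low. If instead sicker people stay more, the error reverses.

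*Adherence markers.* In a simulation of 300,000 participants, a marker related to drop-out but not to relapse had AUC 0.499 to 0.502 when scored per attended 3-month interval. Annual attrition was set at 20% or 40%, and the drop-out hazard ratio at 1.5 to 3 per SD. Drop-out was independent of relapse given the marker. Under that condition this reading creates no adherence artefact.

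**Reading B: one label per participant over 2 years, drop-outs labelled by what was seen.**

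- 2-year risk: 1 − exp(−0.801) = 55.1%.
- Mean risk in people leaving uniformly over 0-2 years: 1 − 0.551/0.801 = 31.2%.
- 20% drop-out: 0.80 × 0.551 + 0.20 × 0.312 = 50.3%; 600 × (0.5511 − 0.5033) ≈ 29 mislabelled.
- 50% drop-out: 0.50 × 0.551 + 0.50 × 0.312 = 43.2%; 600 × (0.5511 − 0.4315) ≈ 72 mislabelled.
- A binary feature with no effect on relapse but 20% against 50% drop-out: odds ratio (0.503/0.497)/(0.432/0.568) = 1.33.

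With exponential drop-out instead, 17% of relapsers are missed at 20% annual attrition and 33% at 40%. In the same simulation the pure adherence marker then reaches AUC 0.536-0.585 and 0.565-0.645 respectively. All attrition figures are assumptions.

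**The case against.** A reader might infer that the plan labels early drop-outs as non-relapsers and so turns markers of adherence into predictors of relapse. The documents do not support that. No section codes a withdrawn participant or a missed assessment as not relapsed; the withdrawal section says only that the data are kept. The assessment-tied windows and the participant random effect point to repeated labels, where the artefact vanishes under the condition given above. The participant-based sample size leaves the other reading open but does not establish it.

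Other points also stand. A binary response is not itself a fault: it is the response of a discrete-time model. Relapse incidence is not a study aim. The plan examines predictors of drop-out and relates usable data to scale scores, which may expose an artefact but does not correct it. Recruitment was raised from 300 to 600 partly because attrition was unknown.

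Two defences carry less weight. The confirmatory interview is meant to help establish relapse onset, but the analysis section does not restrict the outcome to confirmed onsets. And although a condensed article may leave row structure and censoring to a fuller plan, this one does state a relapse definition, an enrolment rule and a missing-data assumption. The concern is how those stated elements fit together.

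**Conclusion.** The point holds in limited form. As written, the outcome is the presence of MDD, in a cohort that may be in an episode at entry and stays in follow-up after relapse, and no at-risk rule is given. The model can therefore learn persistence. The size depends on episode length, which the documents do not give: half of an episode's positive rows are not onsets if it spans two assessments, two thirds if it spans three. Separately, relapse-related drop-out is acknowledged but lies outside the stated missing-data method. Its direction is uncertain, because the Discussion allows for both more and less participation among sicker people.

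The observed risk of 43-50%, the 29-72 mislabelled participants and the odds ratio of 1.33 belong only to one label per participant. They rest on a constant hazard, everyone at risk from entry and an assumed 20-50% uniform drop-out. They should not be cited as consequences of the plan as it stands.

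**What to change.** Specify the relapse model as a discrete-time model:

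1. One row per 3-month interval with a completed IDS-SR/CIDI-SF, a logistic or complementary log-log link, and interval as a covariate. LASSO selection remains possible.
2. For the analysis, participants enter or re-enter the risk set only when not in a current episode, using the remission definition already in *Secondary outcomes*. State how people who meet neither the relapse nor the remission definition are handled.
3. Censor at the last completed assessment, and never code a missed assessment as not relapsed.
4. Add a sensitivity analysis for relapse-related drop-out: inverse-probability-of-censoring weights, or drop-out counted as relapse as a bounding case.
5. Count the 100-event target in the same unit.

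The change uses data already collected on the existing schedule. It costs analysis-plan wording, somewhat more data preparation and fewer intervals counted as events, so the number of candidate variables should be checked against the onsets that remain.

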## Discussion

There is substantial evidence to suggest that changes in physical activity, sleep, stress, prosodic features, cognitive function, mood and sociability are associated with an increased risk of relapse [9–13]. RMT provides a new and unobtrusive way of measuring these variables, using smartphones and wearable technology to collect data reflective of participants’ daily lives and clinical symptoms. RADAR-MDD is the largest study to investigate multimodal RMT in a clinical cohort. If RADAR-MDD demonstrates that RMT is feasible to use in large populations, acceptable for participants, and provides clinically useful data, it may represent that start of a paradigm shift in how clinical data are collected and respective change in how health services are delivered [54]. The RADAR-CNS platform is a device-agnostic system and could be applied to any diagnosis or incorporated into any study design, potentially transforming data collection for clinical and research purposes.

However, to ensure translation into health services, extensive work is required to identify the RMT biosignatures most useful to assist in early detection of deterioration, and to understand the potential barriers and facilitators of large-scale uptake. There are anticipated challenges to this novel method of data collection. Firstly, change in health status may be a key barrier to long-term engagement with this study [30]; an exacerbation of depressive symptoms may influence ongoing participation rate throughout the duration of follow-up, and participant drop-out may represent a depressive relapse. However, there is also some evidence to suggest that people experiencing more severe symptoms may participate more fully, as they may be more motivated to improve their understanding of their condition [55]. Secondly, whilst this is a non-interventional study, encouraging individuals to monitor their own health and providing feedback on activity and sleep (via the FitBit app) may prompt people to change their behaviours or seek help sooner, reducing risk of relapse. There is also evidence to suggest that encouraging health monitoring may increase health anxiety, which in turn may contribute to worsening depressive symptoms [31].

There are clear challenges to overcome, and RADAR-MDD hopes to identify as many of them as possible through qualitative interviews and intensive follow-up procedures and provide some insight into how to overcome these barriers for future implementation of RMT procedures. There are also important future benefits of this method of data collection. The data are inherently personal, and providing personalised feedback may increase individuals’ health awareness and facilitate self-management behaviours to improve long-term health outcomes [56]. Furthermore, RMT may provide a solution to traditional reliance on infrequently measured subjective outcomes in clinical trials, which can lead to imprecision, inefficiency, and the need for larger sample sizes.

RADAR-MDD is an essential step towards improving our understanding of the feasibility and acceptability of large-scale RMT data collection and determining the clinical utility and predictive ability of RMT to predict relapse in major depressive disorder.

## Abbreviations

AE: Adverse event
aRMT: Active remote measurement technology
AUDIT: Alcohol use disorders identification test
BIPQ: Brief Illness perceptions questionnaire
CIBER: Centro de investigacion biomedican en red
CIDI-SF: Composite international diagnostic interview - self Report
CSRI: Client service receipt inventory
DSM: Diagnostic and statistical manual
ESM: Experience sampling method
GAD7: 7-item generalised anxiety disorder questionnaire
GPS: Global positioning system
IDS-SR: Inventory of depressive symptomatology- self-report questionnaire
LIDAS: Lifetime depression assessment – self-report
LTE-Q: List of threatening experiences – questionnaire
MDD: Major depressive disorder
PHQ8: 8-item patient health questionnaire
pRMT: passive remote measurement technology
PSSUQ: Post-Study system usability questionnaire
RADAR-CNS: Remote assessment of disease and relapse - central nervous system
RADAR-MDD: Remote assessment of disease and relapse - major depressive disorder
REDCap: Research electronic data capture
RMT: Remote measurement technology
RSES: Rosenberg self-esteem scale
TAM-FF: Technology assessment model fast form
VUmc: Vrije Universiteit Medisch Centrum
WSAS: Work and social adjustment scale
